## Abstract

**Background:**

Pain is one of the most frequent problems among patients diagnosed with cancer. Despite the availability of effective pharmacological treatments, this group of patients often receives less than optimal treatment. Research into nurses' pain management highlights certain factors, such as lack of knowledge and attitudes and inadequate procedures for systematic pain assessment, as common barriers to effective pain management. However, educational interventions targeting nurses' pain management have shown promise. As cancer-related pain is also known to have a negative effect on vital aspects of the patient's life, as well as being commonly associated with problems such as sleep, fatigue, depression and anxiety, further development of knowledge within this area is warranted.

**Methods/design:**

A quasi-experimental study design will be used to investigate whether the implementation of guidelines for systematic daily pain assessments following a theory-based educational intervention will result in an improvement in knowledge and attitude among nurses. A further aim is to investigate whether the intervention that targets nurses' behaviour will improve hospital patients' perception of pain. Data regarding nurses' knowledge and attitudes to pain (primary outcome), patient perception regarding pain (secondary outcome), together with socio-demographic variables, will be collected at baseline and at four weeks and 12 weeks following the intervention.

**Discussion:**

Nursing care is nowadays acknowledged as an increasingly complicated activity and "nursing complexity is such that it can be seen as the quintessential complex intervention." To be able to change and improve clinical practice thus requires multiple points of attack appropriate to meet complex challenges. Consequently, we expect the theory-based intervention used in our quasi-experimental study to improve care as well as quality of life for this group of patients and we also envisage that evidence-based guidelines targeting this patient group's pain will be implemented more widely.

**Trial Registration Number:**

ClinicalTrials.gov NCT01313234

## Background

Pain is one of the most common problems among patients suffering from cancer [1]. Despite the availability of effective pharmacological treatments and the fact that 70 - 90% of the patients can gain pain relief with the correct pain management, this group often receives less than optimal treatment [2-7]. This is demonstrated, for example, in one of the most extensive studies performed in Europe (EPIC), which found that 43% of the Swedish patients experienced cancer-related pain, 18% of whom did not receive any pain-relieving medication, despite grading their pain as moderate to severe on the Visual Analogue Scale (VAS ≥ 5) [8]. In a Meta-analysis (52 studies included) by van den Beuken and colleagues [1] investigating the prevalence of cancer-related pain, 64% of those with advanced cancer, 59% of those receiving cancer treatment and 33% of those after treatment experienced some degree of pain. Additionally, more than one-third graded their pain as moderate to severe [1]. These studies consequently imply that there is still some work that needs to be done for nurses within the area of cancer-related pain management. Furthermore, we know that cancer-related pain can have a negative impact on several vital aspects of the patient's life and cancer-related pain is commonly associated with other problems, such a sleep, fatigue, depression and anxiety [9,10]. Subsequently, cancer-related pain is an important problem to target in health service research. In-depth interviews [8] have shown that patients sometimes experience their cancer-related pain as being so difficult that they say they "would rather die" and that their nurse or doctor never or rarely asks them about their pain. All of the above are serious issues, which are prone to result in reduced quality of life for this group of patients. Interventions targeting the implementation of acceptable pain management in clinical practice are thus critical in the nursing care of these patients.

Studies investigating barriers to adequate pain management among registered nurses (RN) have identified lack of knowledge of cancer-related pain and pain treatment [11,12] as a serious obstacle to acceptable pain relief. The RNs' attitude to pain and pain treatment, i.e. their own subjective judgement about the patient's pain, such as reliance on non-verbal behaviour as a pain indicator, has also been shown to impede appropriate pain management [13]. Research identifies other plausible explanations for inadequate treatment of cancer-related pain, such as insufficient routine procedures for systematic measurement and assessment of pain [14,15]. Consequently, the introduction of pain assessment instruments has been shown to reduce the impact of pain on patients' daily lives as well as improving how they manage their pain [16]. The Swedish Society of Nursing has developed national guidelines for pain assessment of cancer-related pain, recommending that pain should be assessed routinely and systematically. Despite the existence of such national guidelines it is not yet standard practice on general hospital wards in Sweden to screen for pain or to systematically assess pain among patients on a daily basis.

Attitudes to and knowledge of pain and its treatment can be improved by means of educational interventions [17,18], and this will also contribute to eliminating the RNs' barriers to pain management [19]. However, when designing educational interventions research indicates that it is important to bear in mind how human nature works in relation to behavioural change [20,21], i.e. change of practice, and that possible positive improvement in behavioural change may not be sustained [17]. It is also well known that education *per se *is not an effective and viable strategy for changing behaviour. Instead, interactive learning in small groups and learning from personal experience have proved to be winning blueprints for change [22]. To successfully bring about behavioural change, the educational strategies also need to enhance feelings of ownership and initiate involvement from those participating.

Our review of the literature has highlighted the importance of a change in nursing practice, but also in attitudes and knowledge among RNs about cancer-related pain management in general. To improve the quality of care in this group of patients further investigations into this complex of problems are thus warranted.

## Methods/Design

### Study questions

1) Will an intervention consisting of the implementation of guidelines on daily systematic pain assessment following a theory-based education, targeting cancer-related pain and pain treatment, lead to a significantly positive improvement in RNs' knowledge and attitudes regarding their pain management?

2). Will the interventions targeting RNs influence hospital patients' perception of their cancer-related pain?

### Study design

This study will be carried out with a quasi-experimental design with non-equivalent control groups (Figure 1). Our rationale for a quasi-experimental design was that this type of design is known to be useful for testing causal hypotheses in field settings. It is acknowledged as a practical and feasible design while providing a systematic framework for answering questions relevant to 'real' clinical practice [23]. The design is also considered to be less intrusive on conditions in natural settings. It is important to acknowledge that due to the lack of randomisation, the intervention and control group may be systematically different. However, as it was not possible within the scope of this study to achieve a true experimental design a quasi-experimental design with non-equivalent control groups where the intervention can be separated from effects due to extraneous variables is preferred [23].

**Figure 1 F1:**
[figure not shown]
**Overview of study design**.

### Setting, sample and sample size considerations

Participants (i.e. patients and RNs) will be recruited from two surgical wards specialising in patients with a cancer diagnosis at a hospital in South East Sweden. The hospital has 370 beds and provides services for approximately 150,000 people in the region. The intervention and control ward (26 beds on each ward) has 70 RNs and each year the wards admit around 820 patients who have been diagnosed with cancer.

Following negotiations on all organisational levels, both wards have agreed to participate in the study. The reason for this optimal numbers of participating RNs (n = 70) is that this study is seen within the organisation as providing support to the staff's annual education slots but also as part of supporting quality assurance of its care provision. Assignment to either the intervention ward or control ward is done by the research team.

Sample size calculations for the primary outcome measured by the Knowledge and Attitudes Survey Regarding Pain (KAS) are based on an expected 4.8 change in scores [24] among the RNs on the intervention ward and no changes among the RNs on the control ward. A significance level ᾳ of 0.05 (two-sided) and a power of 80% would require 33 RNs per group. Sample size calculations for the secondary outcome measure, the BPI-SF are based on the expectancy of a 1, 8 point decrease in total score regarding item current pain intensity among the patients on the intervention ward compared to the patients on the control ward [25]. Based on a significance level ᾳ of 0.05 (two sided) and a power of 95% this would require 30 patients per group.

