#### Outcome parameters

##### Primary outcome measure

Our primary outcome will be RNs' attitude and knowledge as measured using a modified version of the KAS [31] at baseline, four weeks and twelve weeks after the intervention for the RNs on the intervention ward (Figure 1). As there is a risk that the RNs on the control ward may be inadvertently exposed to the interventions, i.e. assessing their patients' pain intensity and pain impact on daily life, the RNs on the control ward will also be assessed at baseline and at twelve weeks to check for exposure biases.

The original KAS consists of 40 items where items 1-22 are false-true statements, items 23-36 are multiple-choice questions and items 37-40 consist of two case studies [31]. KAS has shown test-retest reliability (r > 0.80) [31] and internal consistency [32] range between 0.70 - 0.73 [31,33]. KAS takes around 10-15 minutes to complete and the number of correct answers is divided by the number of items (38) to produce the percentage of the total score [31]. We have removed two items as they were considered to be context-specific for the instrument's country of origin. The instrument has not been used in Sweden previously, hence a back translation by an authorised translator from English to Swedish was made.

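### The research team chooses which of two consenting wards is trained, an avoidable source of directional bias that a random draw after baseline KAS would remove only in expectation

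*Protocol article*

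**What the plan says.** All references are to the protocol article.

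- **Setting, sample and sample size considerations.** Participants are "recruited from two surgical wards specialising in patients with a cancer diagnosis", so each arm is one ward. After negotiation, "both wards have agreed to participate in the study". The same paragraph ends: "Assignment to either the intervention ward or control ward is done by the research team". It gives neither a criterion nor a random method.
- **Study design.** The study is declared a "quasi-experimental design with non-equivalent control groups". The authors concede that "due to the lack of randomisation, the intervention and control group may be systematically different", and justify the design by saying that "it was not possible within the scope of this study to achieve a true experimental design".
- **Primary outcome measure.** KAS is taken at baseline, four and twelve weeks on the intervention ward, and "the RNs on the control ward will also be assessed at baseline and at twelve weeks". The text does not place the baseline survey before or after the assignment of wards.
- **Statistical analysis.** The groups are to be compared at baseline and at end of study, with univariate and multivariate techniques, on outcomes, demographics, diagnosis, age, and the nurses' experience and education.

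**The concern.** Once both wards have consented and the whole ward is the unit assigned, a random choice between them needs no further ward, no further consent and no randomisation of individual nurses. Leaving the choice to the team that runs the study opens the possibility that the ward judged more receptive, and so more likely to improve, receives the programme.

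Such a choice would bear on the primary comparison. Receptiveness affects how much a ward changes, not only where it starts. KAS is measured once before the intervention, so differing trends between the wards cannot be seen or adjusted for, and none of the listed covariates measures readiness to change. The sample size calculation assumes no change on the control ward, so any extra improvement that the intervention ward would have shown anyway counts as programme effect. If nurses also know their ward's assignment when they fill in the baseline KAS, that knowledge could influence their answers.

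**Working it through.** **Inputs from the article:** expected difference 4.8 KAS points (change on one ward, none on the other), two-sided α 0.05, power 80%, 33 nurses per group, 70 nurses in all, two wards.

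**Assumptions:** the nurses split equally, 35 per ward; a ward difference *w* in KAS change that would exist without the programme (1, 2 or 3 points); a nurse-level two-sided z-test that ignores ward.

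**Step 1: the plan's own figure.** No SD is stated, so 33 per group can be matched only by solving for the SD:

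SD = 4.8 / (1.960 + 0.842) × √(33/2) = 6.96. A t-test calculation gives 6.85. The SD is therefore about 6.9.

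**Step 2: rejection rates with no programme effect.**

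SE = 6.96 × √(2/35) = 1.664.

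- Probability of a significant result in favour of the ward that improves more: A = 1 − Φ(1.96 − w/SE).
- Probability of a significant result in favour of the other ward: B = Φ(−1.96 − w/SE).
- The two-sided false-positive rate is A + B, whichever ward is trained.
- False benefit (a significant result in favour of the trained ward) is A if the favourable ward is always picked, and (A + B)/2 under a draw.

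| w | w/SE | A: favourable ward picked | B | A + B: two-sided, any assignment | (A + B)/2: draw |
|---|---|---|---|---|---|
| 1 | 0.601 | 0.087 | 0.005 | 0.092 | 0.046 |
| 2 | 1.202 | 0.224 | 0.001 | 0.225 | 0.113 |
| 3 | 1.803 | 0.438 | <0.001 | 0.438 | 0.219 |

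Against the 4.8-point target, 1 and 2 points are 1/4.8 = 21% and 2/4.8 = 42%.

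**Step 3: sensitivity.** With 33 per ward and SD 6.85, a t-test gives two-sided rates of 0.090 and 0.215 at 1 and 2 points, almost the same. The SD matters more. With 35 per ward and *w* = 2, an SD of 5 gives SE = 5 × √(2/35) = 1.195 and false benefit of 0.39 (favourable ward picked) against 0.19 (draw). An SD of 10 gives SE = 2.390 and 0.13 against 0.07. In each case the draw roughly halves the chance of a false benefit.

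**Step 4: what the draw leaves in place.** With two wards there are only two possible assignments, so a randomisation test cannot give a one-sided p below 0.5. The realised bias after a draw is still +w or −w; only its average is zero. If ward effects are random, the nurse-level test after a draw has a type I error of 9%, 13%, 24% and 37% at assumed intraclass correlations of 0.01, 0.02, 0.05 and 0.10, against the nominal 5%.

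**The case against.** The strongest reply is that this is a declared design and not a slip. The Study design section calls the groups non-equivalent, admits that they may differ systematically and says that a true experiment was not feasible. Assignment by the team is compatible with that, so there is no contradiction and no hidden error. This stands. However, the feasibility statement is general and gives no reason against a draw between two wards that have both agreed. A draw could be made without claiming a true experiment.

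Three stronger readings are tempting, and the document does not support them.

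- **That a draw would remove the allocation bias.** It removes only the systematic direction that comes from the team's choice. The two-sided false-positive rate of about 9% or 22% belongs to the ward difference itself and is the same whichever ward is trained, so it cannot be presented as what the draw repairs.
- **That the team favoured a motivated, better staffed or more convenient ward.** The article does not compare the wards on any of these. A team could equally choose the ward in greater need, which might push the bias the other way.
- **That assignment was known before the baseline KAS.** This would be an inference from silence, and the design overview in Figure 1 is not available here.

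It can also be said that the baseline comparison and multivariate analysis handle part of the problem. They may reduce differences in measured characteristics but do not remove a difference in trend. Finally, a condensed article may leave the basis of the choice to the full protocol, so its absence is not itself a finding.

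**Conclusion.** The point holds as an avoidable design weakness. The article states how the wards are assigned, by the research team, where a draw was open to it at almost no cost. The gain from a draw is limited. Under assumed ward differences of 1 and 2 KAS points, the chance of a false benefit falls from about 9% and 22% to about 5% and 11%. That compares a draw with the worst case, in which the favourable ward is certain to be picked; if the team's choice is unrelated to prospects of improvement, there is no such gain. The figures rest on a back-solved SD, an equal split of the 70 nurses and assumed ward differences. A biased choice is a risk, not something shown to have happened. Ward and intervention remain fully confounded after a draw, and that is the larger limit on what the study can conclude.

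**What to change.** Replace the assignment sentence in Setting, sample and sample size considerations with wording such as: *After the baseline KAS has been completed on both wards, the intervention ward will be chosen by a documented random draw made by a person outside the research team.* This removes the team's discretion and ensures that baseline answers are given before the assignment is known.

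Keep the limitation from the Study design section and sharpen it: with one ward per arm, a difference in KAS change cannot be separated from a difference between the wards, draw or no draw, and the conclusions must say so.

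The cost is one sentence and a short draw. The small downside is that workshop rosters can be fixed only afterwards.

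### With one ward per arm the intervention cannot be separated from the ward, and the stated 80% and 95% power hold only if there is no ward-level variation

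*Protocol article*

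**What the plan says.** In the Protocol article, Setting, sample and sample size considerations, participants "will be recruited from two surgical wards specialising in patients with a cancer diagnosis" at a single hospital. One ward receives the intervention and the other usual care: "Assignment to either the intervention ward or control ward is done by the research team". On staffing: "The intervention and control ward (26 beds on each ward) has 70 RNs".

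The KAS sample size is "based on an expected 4.8 change in scores [24] among the RNs on the intervention ward and no changes among the RNs on the control" (usual-care) ward. At a two-sided 5% level, "a power of 80% would require 33 RNs per group". For the BPI-SF item on current pain the expected difference between wards is 1.8 points, and "a power of 95% this would require 30 patients per group". The section gives no SD, ICC, design effect or ward term.

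The Study design section concedes that the groups may differ systematically because they are not randomised. It then says that "a quasi-experimental design with non-equivalent control groups where the intervention can be separated from effects due to extraneous variables is preferred". The Statistical analysis section plans univariate and multivariate comparisons between the two groups.

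**The concern.** The intervention works on the ward as a whole: its nurses are trained together and pain assessment becomes a required routine there. Whatever else happens on only one of the wards during follow-up, such as a change of manager, staffing or another quality project, falls on the same contrast as the intervention. No analysis of these data can pull the two apart.

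A second consequence of the same design is that people on one ward may resemble each other, or change together. The power is stated as if the number of individuals alone fixed the precision.

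Study question 1 asks whether the intervention will lead to improvement, and the article says the findings will be used to update guidelines. A significant result would therefore be read as a causal effect at 5% error, found with 80% or 95% power. The design does not secure that reading.

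**Working it through.** **Inputs from the article.** Two wards, one per arm. KAS: difference 4.8, two-sided 0.05, power 80%, n = 33 per group. BPI-SF current pain: difference 1.8, two-sided 0.05, power 95%, n = 30 per group. **Assumed:** ICC of 0.01, 0.05 and 0.10, because the article gives none. For an analysis of KAS change, read this as the ward-by-time ICC.

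**1. The plan's own figures.** They cannot be reproduced forwards, because no SD is stated. Solving the independent two-sample formula backwards, SD = difference / [(z for alpha + z for power) × sqrt(2/n)]:

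- KAS: 4.8 / [(1.960 + 0.842) × sqrt(2/33)] = 4.8 / 0.690 = 6.96 (6.85 with the t distribution)
- BPI-SF: 1.8 / [(1.960 + 1.645) × sqrt(2/30)] = 1.8 / 0.931 = 1.93 (1.90 with the t distribution)

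The figures are thus consistent with independent observations and SDs of about 6.9 and 1.9.

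**2. Degrees of freedom for wards.** 2 wards − 2 arm means = 0. Between-ward variance cannot be estimated, whatever the number of nurses or patients.

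**3. Effect of ward-level variation.** With one ward per arm:

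- Var(difference) = 2 × SD² × [ICC + (1 − ICC)/n] = (2 × SD²/n) × DE, where DE = 1 + (n − 1) × ICC
- Power, with the ICC treated as known = Phi[(z for alpha + z for power)/sqrt(DE) − 1.96]
- The naive test takes its standard error from within-ward spread, which is too small by the factor r = sqrt[DE/(1 − ICC)]. Its type I error is 2 × [1 − Phi(1.96/r)].

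Example, KAS at ICC 0.05: DE = 1 + 32 × 0.05 = 2.60. Power = Phi(2.802/1.612 − 1.96) = Phi(−0.22) = 41%. r = sqrt(2.60/0.95) = 1.654, and type I error = 2 × [1 − Phi(1.185)] = 24%.

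| Outcome | ICC (assumed) | DE | Effective n per ward | Power | r | Type I error |
|---|---|---|---|---|---|---|
| KAS, 33 per ward | 0 | 1 | 33 | 80% | 1 | 5% |
| | 0.01 | 1.32 | 25.0 | 68% | 1.155 | 9% |
| | 0.05 | 2.60 | 12.7 | 41% | 1.654 | 24% |
| | 0.10 | 4.20 | 7.9 | 28% | 2.160 | 36% |
| BPI-SF, 30 per ward | 0 | 1 | 30 | 95% | 1 | 5% |
| | 0.01 | 1.29 | 23.3 | 89% | 1.142 | 9% |
| | 0.05 | 2.45 | 12.2 | 63% | 1.606 | 22% |
| | 0.10 | 3.90 | 7.7 | 45% | 2.082 | 35% |

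A simulation of the naive t-test (40,000 runs per setting) gave type I errors of 8.8% / 23.5% / 36.0% for KAS and 8.3% / 21.8% / 34.0% for BPI-SF, within one percentage point of the formula.

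**4. Would more participants help?** As n grows, Var(difference) falls only to 2 × SD² × ICC. At ICC 0.05 the power ceiling is Phi(0.690/sqrt(0.10) − 1.96) = 59% for KAS and Phi(0.931/sqrt(0.10) − 1.96) = 84% for BPI-SF. At ICC 0.01 the KAS power could be restored with 49 nurses per ward if that ICC were known, but the two wards have 70 nurses in all.

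**The case against.** **The article is open about non-randomisation.** It says the groups may differ systematically, that a true experiment was not possible within the scope of the study, and that measured characteristics will be compared and used in multivariate analysis. This stands in part: adjustment can deal with measured case-mix and nurse experience. It cannot deal with what happens on one ward only. The caveat also does not mention that ward and intervention coincide, and the sentence that follows it claims separability.

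**Baseline measurement removes ward differences.** This stands for stable differences in KAS, which is measured on both wards at baseline and twelve weeks. A reader might infer that any difference between the wards invalidates the comparison. The article does not support that, because only ward-specific change during follow-up matters for KAS, and its ICC may be smaller. For patients the defence is weaker. The Secondary outcome measure section places both the admission and the discharge BPI-SF after the education, so no pre-intervention ward level is available. (The Abstract mentions a baseline for patient perception, but the section that sets out the assessments does not provide one.)

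**The sample sizes may already include clustering.** A reader might infer that the figures reproduce only under independence. That is not shown, because the SD is free: DE 2.60 with SD 6.96/sqrt(2.60) = 4.32 fits 33 per group equally well, and DE 2.45 with SD 1.93/sqrt(2.45) = 1.24 fits 30. Independence is the natural reading when no design effect is mentioned, but it remains an inference. The loss of degrees of freedom does not depend on it.

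**This could be left to an analysis plan.** The power and separability statements are made in this article, and no analysis can estimate ward variance from one ward per arm.

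**Conclusion.** The point holds as a conditional one. Ward and intervention are completely confounded because there is one ward per arm; this does not follow from the power formula and would remain under any power calculation. The separability statement in the Study design section is therefore not supported.

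The 80% and 95% carry no visible allowance for clustering and are right only if ward-level variation is zero. The size of the departure is unknown. The table in the working illustrates it under assumed ICCs of 0.01 to 0.10 and the implied SDs of about 6.9 and 1.9. It does not estimate this trial's error rates. A reader might infer that the stated rates are shown to be wrong. The article gives no ICC, so it shows only that they are unprotected.

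**What to change.** 1. Study design: delete the statement that the intervention can be separated from extraneous variables. Say instead that ward and intervention coincide.
2. Setting, sample and sample size considerations: state that both powers assume zero ward-level variation (for KAS change, zero ward-by-time variation). Show the range of power and type I error for ICC 0.01, 0.05 and 0.10, labelled as assumption.
3. Statistical analysis: report the naive confidence interval, with a sensitivity analysis that widens it for the same assumed ICCs. With 33 and 30 per ward, r in the table is the multiplier for the naive standard error; recompute it for the numbers actually analysed. Say that the data cannot inform the choice of ICC.
4. Word the conclusion as a comparison of two wards and not as a causal effect established at 5% error.

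Keep the sample as it is. Only more wards per arm would make ward variance estimable, and this fix does not ask for that. The cost is some wording and a few lines of sensitivity analysis. The downside is that the stated power and the strength of the conclusion become less favourable.

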### Inclusion criteria

We will include all RNs on the control ward and intervention ward in accordance with what is stated above. We will include patients with a cancer diagnosis who are aged 18 years and older and who are cognitively intact and able to communicate verbally. We will establish the presence of cancer-related pain for the last 24 hours using the VAS [26] at time of admission or no later than within the first 24 hours following admission. Patients with a score of > 1 on the VAS will be invited to participate.

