##### (2) The implementation of guidelines concerning daily systematic pain assessments

Guidelines for pain management and systematic pain assessment will be implemented on the intervention ward immediately following the educational intervention. The daily pain assessment will be integrated as a required standard parameter together with the ordinary routine vital parameters such as temperature, pulse and blood pressure. Routine vital parameters on the wards are performed by RNs representing three different work shifts and pain will thus be assessed by the VAS at three points in time i.e. 4 am - 6 am, 1 pm - 3 pm and 7 pm - 9 pm. Pain intensity, nursing action and nursing follow up will be documented in the patient-specific study protocol at the bedside.

VAS is an instrument consisting of a 10 cm horizontal line, which measures pain intensity from "no pain to "worst pain imaginable". Patients participating in the study will be asked to assess current pain intensity by marking the line between the two extremes [26]. The average test-retest coefficient across four studies involving adults with cancer-related pain was r = 0.80 [29]. VAS can be used as a regular, short-term assessment instrument for pain intensity as well as an evaluation of ongoing pain treatment [30].

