##### Secondary outcome measure

We will measure pain intensity and pain impact on daily life among the patients using the Brief Pain Inventory - Short Form [34]. The patient assessments by BPI-SF on admission (or no later than 24 hrs after admission) to the wards (intervention ward and control ward) and on discharge from the wards will follow directly after the educational intervention for the RNs on the intervention ward and control ward (Figure 1). The BPI-SF will be undertaken by the RNs admitting, discharging and/or responsible for the patient. Our rationale for including assessments of the patients on the control ward is our wish to rule out competing explanations for results obtained [23], i.e. a positive change in the patients' pain perception on the intervention ward. Hence, both groups will be compared in terms of secondary outcome, demography and diagnosis.

BPI-SF is a pain assessment instrument developed for cancer patients [34]. It is widely used and demonstrates sound psychometric properties [2,4,35-42]. The Swedish version has been linguistically validated but has not yet been psychometrically validated [43]. The instrument consists of nine items, as well as a figure depicting a human body where the patient marks the location and type of pain. BPI-SF includes items relating to the current degree of pain, pain during the last 24 hours and pain on average, as well as items related to the effect of pain treatment, walking ability, mood, work, relationships and whether sleep is affected by pain [34].

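### The patient sample size rests on a score that mixes a total with the single current-pain item, and that item does not match the 24-hour pain window used for entry

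*Protocol article*

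**What the plan says.** All places are in the protocol article.

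- **Setting, sample and sample size considerations.** The patient calculation assumes a 1.8-point "decrease in total score regarding item current pain intensity among the patients on the intervention ward compared to the patients on the control ward", with a literature reference for the figure. It uses a significance level "of 0.05 (two sided) and a power of 95% this would require 30 patients per group". No SD is given.
- **Inclusion criteria.** "We will establish the presence of cancer-related pain for the last 24 hours using the VAS", at admission or within 24 hours of it. "Patients with a score of > 1 on the VAS will be invited to participate". No level of current pain is required.
- **Secondary outcome measure.** The outcome is described as pain intensity and impact on daily life, measured with the BPI-SF at admission and discharge. The instrument is said to cover "items relating to the current degree of pain, pain during the last 24 hours and pain on average", plus effect of treatment and interference. No single score is picked out.
- **Statistical analysis.** The BPI-SF is compared between the wards at baseline and at end of study by univariate and multivariate techniques. Adjustment of the discharge value for the admission value is not mentioned.
- **Study design.** The control group is described as non-equivalent, and the authors accept that the groups may differ systematically.

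**The concern.** Two things do not fit together.

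First, the powered quantity is worded as both a total and one item. A reader cannot tell for certain whether the 1.8 points refers to the current-pain item, to an intensity composite, or to the questionnaire as a whole. The section that should settle this lists several candidate scores and ranks none. If the wording stays open, the choice of score is less protected against being made once the data are known.

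Second, on the most natural reading (the current-pain item), entry and outcome look at different time windows. A patient with intermittent pain, or whose pain has been relieved by the time the admission BPI-SF is taken, can satisfy the 24-hour entry rule and still score 0 or 1 on current pain. Such a patient has little room to fall on that item. If there are many of them, the average difference between wards could be smaller than planned.

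**Working it through.** **Inputs.** From the sample size section: difference 1.8 points, two-sided α = 0.05, power 95%, 30 per group. The SD is not stated. The share of patients without current pain at admission is not stated either; 10%, 25% and 40% are assumed below for illustration.

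**Step 1: what 30 per group implies.**

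Normal approximation: SD = 1.8 × √(30/2) / (1.960 + 1.645) = 1.8 × 3.873 / 3.605 = 1.93.

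Two-sample t-test: 30 per group with 95% power needs a standardised difference of 0.947, so SD = 1.8 / 0.947 = 1.90.

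So 30 per group is internally consistent if the SD is about 1.9. It cannot be reproduced independently because no SD is printed.

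**Step 2: entry rule beside powered item.**

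| | Entry | Powered quantity |
|---|---|---|
| Instrument | VAS (10 cm line) | BPI-SF |
| Window | last 24 hours | current pain (if the item is meant) |
| Level | above 1 | 1.8-point mean difference between wards |

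The article itself lists current pain and last-24-hour pain as different BPI-SF content. The entry rule therefore allows a current-pain score of 0 at admission. It does not say how often this would happen.

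**Step 3: illustration of dilution.** Suppose a share f of patients shows no change on the item, and 1.8 is the mean effect in the others. The mean difference is 1.8 × (1 − f). Two versions of the SD bracket the result:

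- (a) SD held at 1.90.
- (b) SD allowed to shrink, because patients with no change also add less variance. The control-ward variance is (1 − f) × 1.90². The intervention-ward variance is (1 − f) × 1.90² + f(1 − f) × 1.8². The SD used is the root of their mean.

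Example for f = 25% under (b): control 0.75 × 3.61 = 2.708; intervention 2.708 + 0.1875 × 3.24 = 3.315; mean 3.011; SD 1.735; standardised difference 1.35 / 1.735 = 0.778.

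| f (assumed) | Mean difference | Power (a) | SD in (b) | Power (b) |
|---|---|---|---|---|
| 0 | 1.80 | 95% | 1.90 | 95% |
| 10% | 1.62 | 90% | 1.84 | 92% |
| 25% | 1.35 | 77% | 1.74 | 84% |
| 40% | 1.08 | 58% | 1.60 | 73% |

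(Two-sample t-test, 30 per group.)

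**Step 4: sensitivity to the SD alone.** With the full 1.8-point difference and 30 per group, power is 93% at SD 2.0, 78% at SD 2.5 and 63% at SD 3.0. These SDs are assumed; the documents give no basis for preferring one.

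**The case against.** The strongest reply has five parts.

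- **The wording may be only loose.** The sentence does name an item, and total score may simply mean that item's score. This is plausible, but the outcome section does not confirm it, so the ambiguity stands. It does moderate the concern about choosing a score after the fact: the text leans towards one item, and ranking of scores may sit in a fuller document that is not shown.
- **Patients without current pain can still contribute.** The planned effect is a contrast between wards. A patient at 0 on admission adds to it if comparable control patients have more pain at discharge, and a patient at 1 can still fall by 1. The 1.8 is a mean difference, not something each patient must achieve. This stands: the limitation is less room to fall on one item, not an inability to benefit.
- **The 1.8 may already include such patients.** It is quoted as an expected group difference from a cited study. If that study's sample contained patients with little current pain, step 3 counts the dilution twice. The documents cannot settle this.
- **A missing SD is normal in an article, and 1.9 may be an adjusted or change-score SD.** This also stands. A raw SD of 2.5 has a residual SD of 1.9 when admission and discharge correlate at about 0.65, since √(1 − (1.9/2.5)²) = 0.65; for a raw SD of 3.0 the correlation is about 0.77. The missing SD is not a fault in its own right.
- **Matching the item to the entry window does not remove the floor.** With entry at VAS above 1, a patient just over the threshold also has less than 1.8 points to lose on a 24-hour item. That is correct; matching removes only the part of the problem that comes from the differing windows.

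**Conclusion.** The point holds as a problem of definition and alignment. The sample size section describes the powered patient outcome in terms that mix a total with one item, the outcome section does not resolve it, and the entry criterion selects on a different time window from the item named.

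A reader might go further and infer that the plan fails to deliver its 95% power, or that patients without current pain cannot improve. The documents support neither. They give no SD and no share of patients without current pain, the cited 1.8 may already average over such patients, and the effect is a between-ward contrast. The ranges of 90–92%, 77–84% and 58–73% for assumed shares of 10%, 25% and 40% show what could be at stake. They are not estimates of the trial's power, and they rest on an SD of about 1.9 in responsive patients and on 1.8 applying only to those patients.

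The matter affects the secondary outcome. The primary outcome, nurses' KAS score, is untouched.

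**What to change.** 1. In the sample size section, replace the mixed phrase with one pre-specified BPI-SF score matched to the entry window, and use the same name in the outcome section. The average-pain item, named alone and with its recall period stated, is one example. Offering average or last-24-hour pain as alternatives would leave the choice open again.
2. Analyse that score at discharge with adjustment for the admission value. The wards are acknowledged to be non-equivalent and the admission value is already collected.
3. Keep current pain and the interference items as supportive.
4. Restate the 1.8 points and the implied SD of about 1.9 as assumptions, and give power over a range of SDs, for example 1.9 to 3.0 as in step 4, noting whether the SD is raw or adjusted for admission.

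The cost is wording and a recomputed power statement, with no new data collection and no change to care. There is one small downside: the cited 1.8 points was for current pain, so for another item it becomes a working assumption.
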